# Postoperative awake prone position in geriatric patients with hip fractures: a protocol for a randomized controlled trial on the efficacy of postoperative prone position in reducing pulmonary complications and improving oxygenation

**DOI:** 10.1186/s13063-023-07308-x

**Published:** 2023-04-18

**Keywords:** Hip fracture, Geriatric, Awake prone position, Postoperative pulmonary complications, Hypoxemia

## Abstract

**Introduction:**

Postoperative pulmonary complications (PPCs) are prevalent in geriatric patients with hip fractures. Low oxygen level is one of the most important risk factors for PPCs. Prone position has been proven efficacy in improving oxygenation and delaying the progress of pulmonary diseases, especially in patients with acute respiratory distress syndrome induced by multiple etiologies. The application of awake prone position (APP) has also attracted widespread attention in recent years. A randomized controlled trial (RCT) will be carried out to measure the effect of postoperative APP in a population of geriatric patients undergoing hip fracture surgery.

**Methods:**

This is an RCT. Patients older than 65 years old admitted through the emergency department and diagnosed with an intertrochanteric or femoral neck fracture will be eligible for enrollment and assigned randomly to the control group with routine postoperative management of orthopedics or APP group with an additional prone position for the first three consecutive postoperative days (PODs). Patients receiving conservative treatment will not be eligible for enrollment. We will record the difference in the patient’s room-air-breathing arterial partial pressure of oxygen (PaO_2_) values between the 4^th^ POD (POD 4) and emergency visits, the morbidity of PPCs and other postoperative complications, and length of stay. The incidence of PPCs, readmission rates, and mortality rates will be followed up for 90 PODs.

**Discussion:**

We describe the protocol for a single-center RCT that will evaluate the efficacy of postoperative APP treatment in reducing pulmonary complications and improving oxygenation in geriatric patients with hip fractures.

**Ethics and dissemination:**

This protocol was approved by the independent ethics committee (IEC) for Clinical Research of Zhongda Hospital, Affiliated to Southeast University, and is registered on the Chinese Clinical Trial Registry. The findings of the trial will be disseminated through peer-reviewed journals.

**Ethics approval number:**

2021ZDSYLL203-P01

**Trial registration:**

ChiCTR ChiCTR2100049311. Registered on 29 July 2021.

**Trial status:**

Recruiting. Recruitment is expected to be completed in December 2024.

**Supplementary Information:**

The online version contains supplementary material available at 10.1186/s13063-023-07308-x.

## Introduction

Given the aging population, the increasing number of geriatric hip fractures has become a tremendous health burden for society globally [1, 2]. For such patients, active surgical treatment has been proven optimal compared with conservative treatment [3]. Geriatric patients are characterized by fragility and multi-comorbidities, which brings a challenge for perioperative management and preoperative rehabilitation [4]. Postoperative complications are always inevitable and impact considerably on the prognosis of geriatric hip fractures [5, 6], among which, postoperative pulmonary complications (PPCs) were the commonest one and the incidence rate was up to 12.6% [7–11]. The PPCs are considered a highly heterogeneous disease group [12]. It usually brought extended length of stays (LOS), increased health care costs, readmission, and even mortality [12–15]. Low oxygen level was one of the independent risk factors of PPCs [16]. Postoperative hypoxemia was persistent and more common than in the preoperative period [17]. Canet et al. pointed out that the morbidity of PPCs would increase significantly if preoperative arterial oxygen saturation (SaO_2_) was less than 90% [13]. Russotto et al. also discovered that the morbidity of postoperative pneumonia (POP) was in liner negative correlation with preoperative SaO_2_ [14]. Moreover, arterial partial pressure of oxygen (PaO_2_) level was a simple predictor of POP with high acceptance in geriatric hip fracture patients and the cut-off value was 72.5 mmHg, which met the standard of hypoxemia (PaO_2_<80mmHg) [18–20].

Nowadays, prone position ventilation was widely applicated in adjuvant therapy for acute respiratory distress syndrome (ARDS), especially secondary to coronavirus disease 2019 (COVID-19), and recommended in the international guideline for the management of critical COVID-19 patients [21]. Recently, prone positioning in non-intubated or awake prone position (APP) characterized by a simple mechanism of action and perceived low risk has also received lots of interest and brought positive effects [22].

For geriatric patients with hip fractures, no widely accepted, long-term, feasible intervention with provable evidence to treat PPCs has been proposed [23, 24]. Lying in the lateral position intra-operatively could improve postoperative PaO_2_/ fraction of the inspired oxygen (FiO2) (P/F) and reduce the need for invasive or non-invasive ventilation in patients with femoral neck fracture (FNF), which remained us change of body position may help to better respiratory function via gas exchange for such patients [25]. We hypothesize that the application of the APP will reduce the risk of PPCs and improve postoperative oxygenation (expressed as P/F) in geriatric patients with hip fractures, an ideal population for randomized controlled trials (RCT).

### Objective

To investigate the hypothesis that the APP would reduce the incidence of PPCs and elevate the room-air-breathing P/F in geriatric patients with hip fractures.

## Method and analysis

### Overview of trial design

We will conduct a single-center RCT using a completely randomized two-arm design to investigate whether APP can decrease the morbidity of PPCs and improve postoperative oxygenation for geriatric patients with hip fractures (Figs. 1 and 2). The Standard Protocol: Items: Recommendations for Interventional Trials (SPIRIT) checklist [26] is provided as Additional file 1. All patients considered for inclusion are admitted from the emergency department to the Trauma and Orthopedic Unit of the Zhongda Hospital affiliated to Southeast University and will be operated by the same team in a fixed operating room. A designated investigator will employ a 1:1 randomization system to assign patients who meet the criteria to the APP group and the control group. Patients enrolled in the study will be followed for at least 90 PODs.

**Fig. 1 Fig1:**
[figure not shown]
Flow chart of study design. *APP* awake prone position, *POD* postoperative day, *PaO*_*2*_ arterial partial pressure of oxygen, *EV* emergency visits, *LOS* length of stay, *PPCs* postoperative pulmonary complications, *CPIS* clinical pulmonary infection score

**Fig. 2 Fig2:**
[figure not shown]
Schedule of enrolment, interventions, and assessments

Patients will undergo a review of hematological parameters including routine blood, biochemistry, electrolyte, and blood gas analysis on POD 4. Clinical pulmonary infection score (CPIS) [27] (Additional file 2) will be calculated on POD 4. The incidence of various postoperative complications, mortality rate, and LOS during hospitalization will be also recorded. At the same time, the incidence of postoperative complications especially PPCs, readmission, and mortality rates will be calculated within 30 and 90 PODs, respectively. This protocol has been approved by the Independent Ethics Committee (IEC) for Clinical Research of Zhongda Hospital, Affiliated to Southeast University (2021ZDSYLL203-P01), and is registered on the Chinese Clinical Trial Registry (ChiCTR2100049311). Only the head of this series of research (YR) has the right to make the final decision to terminate the trial if any serious adverse event judged to be related to the study treatment occurs.

### Primary research question

In geriatric patients with hip fractures, will the addition of APP to routine postoperative treatment reduce the risk of developing PPCs?

### Secondary research question

In geriatric patients with hip fractures, will the addition of APP to routine postoperative treatment result in:Improved postoperative oxygenation?Shorter LOS?Decreased incidence of other kinds of postoperative complications, readmission, and mortality rates?

### Hypothesis

Compared with the control group, geriatric patients with hip fractures who receive postoperative APP treatment will have a lower incidence of PPCs and an improved postoperative oxygenation.

### Setting and participants

Geriatric patients (over 65 years old) presenting to the emergency department with an acute hip fracture from September 1, 2021, to December 31, 202,4 will be admitted to the Trauma and Orthopedic Unit of the Zhongda Hospital affiliated to Southeast University. Before admission, trauma center physicians will take the patient's medical history, risk assessment, physical examination, and necessary laboratory and imaging tests. According to inclusion and exclusion criteria, patients will be screened for eligibility and enrolled as potential participants by one investigator (YG).

Once confirmed to receive surgical treatment, one research implementer (YG) will obtain informed consent from potential participants to take part in the study by means of conversation and sign the approved IEC informed consent forms. All patients will understand that depending on the randomization results, they may or may not receive a postoperative APP. The total number of hospitalized patients who meet the inclusion and exclusion criteria exceeds the minimum sample size required for the study. However, some patients may hesitate to participate in the study due to concerns about the safety of APP and follow-up support of the related unexpected events. To attract more potential participants for the study, we will inform patients of the following during the conversation: firstly, the application of APP after hip fracture surgery in elderly patients has been shown to be safe in the previous attempt; secondly, APP may have a positive effect on preventing postoperative complications and accelerating postoperative recovery; finally, in the event of any unexpected adverse events, the hospital will assume full responsibility for resolution. Participants in the study are voluntary, and if they refuse, their decision will not affect any other aspect of their care. Patients will have the right to learn any details of the intervention and to withdraw from the study at any point.

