### Intervention

After signing informed consent, participants will be enrolled and randomly assigned to either the APP group or the control group. Surgical treatment will be performed on an emergency basis upon completion of the necessary pre-operative preparations. The surgical procedures, including closed reduction and internal fixation, THA, and HHA, will be decided by the chief physician (HC and YR) in trauma orthopedics. All operations will be scheduled in a fixed operating theatre and completed by the same team. Patients in the APP group will receive the prone position for at least half an hour at a time, and at least once per day for the first three consecutive PODs. The first APP treatment each day will be guided and supervised. The frequency and duration of other spontaneous prone positions of patients in the APP group will not be constrained. Except for this, during this period, all patients will receive the same postoperative management including postoperative oxygen inhalation (2L/min) for 6 h, standardized nutritional support, anti-inflammatory, detumescent, analgesic, hypodermic anti-coagulant prophylaxis, and regular atomization therapy. Both FNF and intertrochanteric fracture patients will roll onto their broken side into a prone position. Prone position pads will be used to suspend the upper abdomen and chest to reduce intra-abdominal and intra-thoracic pressure, allowing the alveoli to expand sufficiently. If severe adverse events such as unbearable pain, suspected prosthesis dislocation or internal fixation failure, chest tightness, and difficulty breathing occur, or the patients report that he/she cannot tolerate the prone position, the intervention should be stopped immediately. The investigators’ department will treat and compensate the patient for any additional injuries resulting from APP treatment. Intervention time as an adherence quantitative indicator and the reasons for intervention termination will be recorded in the database. Hematological parameters and chest radiography will be re-examined on the morning of POD 4. Patients will be followed up for at least 90 PODs through outpatient visits or telephone calls. In addition to orthopedic-related tests, they will undergo chest CT in an outpatient setting to determine if PPCs are present. The conduct of the trial will be audited weekly, independently of the investigators.

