### Clinical application of prone position treatment

Previous researches have shown that prone position ventilation may reduce the incidence of ventilator-associated pneumonia, but does not reduce mortality in patients with acute respiratory failure and may increase the risk of other complications such as pressure ulcers [44, 45].

However, there still existed a growing body of clinical evidence supporting that the prone position is of positive significance in delaying the progress of pulmonary diseases and improving prognosis. Compared with the left lateral position, patients who underwent thoracoscopic esophagectomy in the prone position had a markedly higher oxygenation index after the surgery, though no significance was found in the PPCs between the two surgical positions [46]. Prone position has been proven to effectively reduce the risk of mortality and length of intensive care unit stay in ventilator-associated pneumonia patients [47]. Moreover, as one of the protective lung ventilation strategies, the prone position could reduce mortality in severe ARDS and acute respiratory failure patients significantly [48–51]. When applicated to conscious patients, the prone position manifested a similar outcome. Early APP combined with noninvasive ventilation or high-flow nasal canula could reduce or delay the need for intubation and the possibility to develop critical patients in moderate to severe ARDS patients with COVID-19 [52, 53]. For acute hypoxia patients, APP was recommended to be carried out early to prevent the worsening of hypoxemia and respiratory failure [41].

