### Prone position in geriatric patients with hip fracture

If there exists evidence from both anatomic physiology theory and clinical practice that the prone position can improve pulmonary function, we believe that its application should not be limited to patients with severe ARDS. Whether pulmonary complications, which are common following fracture, can be prevented by prone position treatment arouses our interest. Unfortunately, so far, to the best of our knowledge, there have been no reports of the prone position treatment being used in the orthopedic field. This trial is an attempt to extend the application of APP to the postoperative management of geriatric patients with hip fractures in the general ward and provide high-quality evidence.

We believe that postoperative APP treatment in elderly patients with hip fractures is feasible according to the following facts: (1) The only absolute contraindications for prone ventilation were unstable rib or spinal fractures [42]. (2) The development and maturity of anti-rotary intramedullary nail and hip joint arthroplasty technology realize the possibility of early pain relief and rehabilitation activities after hip fracture surgery. (3) No possible complications such as prosthesis dislocation and internal fixation failure occurred in 42 patients arranged in the APP group in our preliminary trials. (4) Improving pulmonary function and physiological status via postural change is better than relying on exogenous oxygen supplements. Moreover, inappropriate exogenous oxygen supplementation could further damage alveolar type II epithelial cells and might cause refractory hypoxemia and respiratory failure [54].

We choose to carry out APP treatment for the first three consecutive PODs to prevent PPCs for the following reasons: 1. The peak time for diagnosis of PPCs and hypoxemia occurred on POD 4 after hip fracture surgery in the elderly [10, 55]. 2. The early postoperative hyperinflammatory state would lead to ALI and increase the risk of pulmonary infection. Animal experiments have shown that elderly rats exhibited the highest pulmonary inflammation level histologically in the first three days following hip fracture fixation. 3. In the first three PODs, the pulmonary infection risk and mortality rate of elderly rats receiving hip fracture fixation reached a peak if inoculating in the airway with Pseudomonas aeruginosa before surgery [56–59].

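### The consent conversation presents prone positioning after hip fracture surgery as shown safe in earlier experience, but no complications in 42 patients cannot show that (exact two-sided 95% upper limit 8.4%)

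*Protocol article*

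**What the plan says.** Under Setting and participants, the protocol article notes that some eligible patients may be reluctant to join because of worries about the safety of APP. It then fixes what they will hear: "To attract more potential participants for the study, we will inform patients of the following during the conversation". The first of the three items is that APP after this surgery "has been shown to be safe in the previous attempt". The second is a hedged statement of possible benefit. The third is that the hospital takes responsibility if something unexpected happens.

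The supporting data are in the Discussion, under Prone position in geriatric patients with hip fracture: "No possible complications such as prosthesis dislocation and internal fixation failure occurred in 42 patients arranged in the APP group in our preliminary trials". The same section says that, to the authors' knowledge, "there have been no reports of the prone position treatment being used in the orthopedic field". No rate, interval or upper bound is given for the 42 patients.

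The Intervention section provides for harm during the sessions: "If severe adverse events such as unbearable pain, suspected prosthesis dislocation or internal fixation failure, chest tightness, and difficulty breathing occur", the session is to be stopped at once.

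**The concern.** The people addressed are those whose doubt is about safety, and the stated purpose is recruitment. For them, the strength of the safety statement bears directly on the decision to take part. A group of 42 patients without an event can rule out a high complication rate. It cannot rule out a moderate one that would matter to a frail patient with a new implant or fixation. Saying that safety has been shown turns the absence of observed events into a conclusion that the number of patients cannot carry. It also asserts in advance something the trial's own adverse-event recording is there to find out.

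**Working it through.** **Inputs**

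- Events: 0, and patients: n = 42 (Discussion, Prone position in geriatric patients with hip fracture).
- Planned APP group: 100 (Sample size consideration).
- Confidence level: not given in the document. I assume 95% and show both two-sided and one-sided limits.
- Identity of the earlier experience: I assume that the attempt mentioned in the consent conversation is the preliminary trials with the 42 patients. The pilot study cited for the sample size is not shown.

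The protocol derives no figure from 0 of 42, so there is nothing of its own to reproduce.

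**Upper limit for the risk**

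With no events among n patients, the exact (Clopper-Pearson) upper limit is the risk at which an event-free series has probability alpha/2 (two-sided) or alpha (one-sided):

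- Exact, two-sided 95%: 1 − 0.025^(1/42) = 1 − 0.9159 = 0.0841, or **8.4%**.
- Exact, one-sided 95%: 1 − 0.05^(1/42) = 1 − 0.9312 = 0.0688, or **6.9%**.
- Wilson, two-sided 95%: z²/(n + z²) = 3.84/(42 + 3.84) = 0.0838, or 8.4%.
- Rule of three: 3/42 = 0.0714, or 7.1%.

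The methods agree on an upper limit of roughly 7% to 8%.

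**How often 42 patients would show nothing**

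The probability of no event is (1 − p)^42. The risks below are illustrations and do not come from the document.

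| True risk p | Probability of 0 events in 42 | Expected cases in 100 patients |
|---|---|---|
| 2% | 0.98^42 = 0.43 | 2 |
| 3% | 0.97^42 = 0.28 | 3 |
| 5% | 0.95^42 = 0.12 | 5 |

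At the upper limits themselves, the planned APP group of 100 would have about 100 × 0.069 ≈ 7 to 100 × 0.084 ≈ 8 affected patients.

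**What the count covers**

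The sentence about the 42 patients names dislocation and fixation failure as examples. It does not say separately whether pain, intolerance, breathing difficulty or pressure injury occurred. It describes patients arranged in the APP group and does not say how many completed the sessions. The limits above therefore apply to complications of the kind named, in patients allocated to APP.

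**The case against.** Several counter-arguments are sound and limit the point.

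- **The claim is qualified.** Its closing words tie it to the earlier experience, so it is not a general statement that APP is safe. That is correct. But the sentence is spoken to reassure new patients, and even as a report of earlier experience, shown to be safe says more than 0 of 42 supports.
- **The consent form is not shown.** Patients sign a form approved by the ethics committee, and may ask for any details of the intervention. A reader might infer that the foreseeable harms go undisclosed. The documents do not support that, because the form may list them. A complete form would still not correct a stronger spoken statement aimed at people with safety doubts.
- **Expectation bias.** A reader might infer that a reassuring script biases the unblinded comparison of pulmonary complications. The documents do not support this as a finding. Both arms hear the same words before randomization, and outcome assessors and analysts are unaware of the grouping. Chest radiography on the fourth postoperative day and chest CT at outpatient follow-up are planned without regard to arm or symptoms.
- **The benefit sentence.** It already says only that APP may help, so there is nothing to correct.
- **Pressure ulcers.** The remark that prone positioning "may increase the risk of other complications such as pressure ulcers" concerns prone ventilation in acute respiratory failure. It should not be carried over to short sessions in awake ward patients as if it were direct evidence.
- **Attribution.** Dislocation and fixation failure also occur without APP. The 8.4% bounds the total risk in such patients, not an excess caused by the position.
- **Scope.** Nothing here changes the endpoint, the sample size or the analysis. That is true, and the remedy is correspondingly small.

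**Conclusion.** The point stands for the safety phrase alone. The protocol commits to telling hesitant patients that safety has been shown. The only direct evidence in the document is 0 of 42, which is compatible with a risk of up to 8.4% (exact two-sided 95% limit) or 6.9% (one-sided). The authors know of no other orthopedic use that could add to it. The protocol's own provision for severe adverse events during sessions sits poorly beside the assurance.

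This rests on two assumptions: that the earlier attempt and the preliminary trials are the same experience, and that 95% is a reasonable level. The choice of one-sided or two-sided limit does not change the conclusion. The result does not mean that APP is harmful or that 8% is a likely value. It means only that 42 patients cannot exclude a risk of that order. The matter is worth correcting because the protocol has recruitment running until December 2024 and the correction protects those still to be approached.

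**What to change.** In the consent conversation, replace the statement that safety has been shown with what was observed and how far it reaches. For example: *no dislocation or fixation failure was seen in 42 earlier patients; this is too few to rule out a risk of up to about 8 in 100.* If the one-sided limit is preferred, the figure becomes about 7 in 100; the authors should settle on one and use it consistently. If the pilot records cover other events or the completion of sessions, report those counts in the same way.

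Make the conversation consistent with the adverse events listed in the Intervention section, so that what patients hear matches what the protocol anticipates. The hedged benefit sentence can stay as it is.

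The cost is a revised script with notification of the ethics committee, and possibly slightly slower recruitment. The protocol states that eligible inpatients outnumber the required sample, which limits that last cost. No change to design, sample size or analysis is needed.
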